#### Study Protocol

The intervention period will last 16 weeks, comprising 3 face-to-face visits for all participants and 2 additional telephone visits for those in the intervention group.

During the baseline visit (visit 1), patients will sign the informed consent, undergo randomization, and have clinical information collected. A complete physical examination will be conducted, and blood samples will be obtained. For patients randomized to the intervention group, this visit will also include the provision of informational materials, the distribution of EVOO, and the initiation of the nutritional intervention.

At week 8, a face-to-face visit (visit 2) will be conducted. The primary objective of this visit is to perform a clinical evaluation to determine if the patient has experienced any clinical worsening that would necessitate the initiation of systemic treatment. If systemic treatment is deemed necessary, the corresponding analytical tests and vaccination protocol will be initiated. This visit at week 8 ensures that participation in the study does not delay the start of systemic treatment if required.

During the final visit (visit 3), clinical information will once again be collected, a complete physical examination will be performed, and final blood samples will be drawn. In addition, feedback will be gathered from the patient regarding their experience in the study, any challenges encountered, and suggestions for improvement. This feedback will be collected through an anonymous, free-response online survey, as well as a brief interview in which the patient can discuss any issues identified during the study with the investigator.

The study protocol is summarized in Figure 1.

**Figure 1 figure1:**
[figure not shown]
Comprehensive overview of the study protocol. As shown, patients in the control group will attend 3 on-site study visits. In contrast, patients in the Mediterranean diet intervention group will attend 3 on-site visits as well as 2 additional remote visits. Participants in the intervention group will receive 4 L of EVOO at weeks 0 and 8 (500 mL per week). Blood tests will be conducted at week 0 and week 16 in both groups. EVOO: extra virgin olive oil; PASI: Psoriasis Area and Severity Index.

#### Outcomes

The primary outcome is the change from baseline in the PASI at week 16. PASI is the most widely used scale for assessing psoriasis severity and informing therapeutic decisions, with scores ranging from 0 (no lesions) to 72 (severe lesions across the entire body surface) [18].

The secondary outcomes include:

Change from baseline in adherence to the MedDiet at week 16: Adherence will be assessed using the validated er-MEDAS questionnaire, which scores from 0 to 17, with higher scores indicating better adherence [17].Change from baseline in anthropometric parameters at week 16: This includes weight, BMI, and abdominal circumference, measured before and after the intervention.Change from baseline in serum inflammatory interleukins at week 16: Levels of various ILs and cytokines will be assessed, including granulocyte-macrophage colony-stimulating factor, interferon gamma (IFNγ), IL-1β, IL 2, IL 4, IL 5, IL 6, IL 9, IL 10, IL 12 (p70), IL 13, IL 15, IL 17A/CTLA8, IL-17E/ IL-25, IL 17F, IL 21, IL 22, IL 23, IL 27, IL 28A/IFNλ2, IL 31, IL 33/NF HEV (mature), MIP-3α/CCL20, tumoral necrosis factor alpha (TNFα), and TNFβ/Lymphotoxin-α (LTA).Change from baseline in metabolic blood parameters at week 16: changes in serum cholesterol, low-density lipoproteins, high-density lipoproteins, lipoprotein A, apolipoprotein A1, apolipoprotein B, fasting serum insulin, hemoglobin, A_1c_ and C-reactive protein (CRP) will be measured.Change from baseline in the impact of the disease on patient’s life at week 16: quality of life will be assessed using the validated questionnaire Dermatology Life Quality Index [18]. Change in sleep quality will be evaluated using the Insomnia Severity Index [19] and emotional state changes will be measured using the Hospital Anxiety and Depression Scale [20].

### Data Analysis

Once data collection is complete, statistical analysis will be performed using StataIC 17 (Stata Corp). A descriptive analysis of the baseline demographic and clinical characteristics of the patients included in the trial will be conducted. Normality will be assessed using skewness, kurtosis, and histogram plots. Parametric variables will be reported as mean (SD), nonparametric variables as median (IQR), and categorical variables as n (%).

To evaluate differences between the intervention groups, statistical significance will be assessed using the Student *t* test for comparing 2 groups and the ANOVA test for comparisons involving multiple groups, for parametric variables. For nonparametric variables, the Wilcoxon rank-sum test and Kruskal-Wallis test will be applied. Pearson chi-square test will be used for categorical variables. An intention-to-treat analysis will be performed.

Linear mixed-effects models will be used to assess changes in nutritional variables from baseline to follow-up visits. Statistical significance will be determined using a 2-tailed level of significance, with *P* values less than .05 considered significant.

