#### Sample Size

There are no previous studies specifically evaluating the impact of MedDiet on skin involvement in patients with psoriasis. The only dietary intervention study in psoriasis to date is by Castaldo et al [8], which reported a decrease in Psoriasis Area and Severity Index (PASI) of 7.2 (95% CI –8.7 to –5.6) in a sample of 37 patients. However, this study differs significantly from MEDIPSO in design; it involved a single group without a control group, used a highly aggressive intervention including prolonged fasting periods, targeted only patients with obesity who have severe psoriasis, and excluded other adjuvant treatments, with a longer follow-up period.

In contrast, our study includes a control group, applies a less aggressive dietary intervention, and focuses on patients with mild-to-moderate psoriasis who are allowed to continue their stable topical treatments. Consequently, we anticipate the SD in PASI reduction at week 16 to be much lower, around 1. To detect a difference of 1 unit on the PASI scale, with an α risk of 0.05 and a  β risk of less than 0.2 in a bilateral contrast, we estimate that 19 participants per group (intervention and control) are needed. We assume a common SD of 1 and estimate a loss-to-follow-up rate of 15%.

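### The primary PASI comparison is left to an unadjusted t test or rank test chosen by an open-ended normality check; one prespecified ANCOVA on baseline PASI would fix the effect measure and usually gain some precision

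*Protocol article*

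**What the plan says.** The Outcomes section defines the endpoint: "The primary outcome is the change from baseline in the PASI at week 16".

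The Data Analysis section does not name PASI. It gives one general rule for comparing the arms:

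- For parametric variables: "To evaluate differences between the intervention groups, statistical significance will be assessed using the Student" t test (ANOVA for more than two groups).
- Otherwise: "For nonparametric variables, the Wilcoxon rank-sum test and Kruskal-Wallis test will be applied".
- The choice between them: "Normality will be assessed using skewness, kurtosis, and histogram plots". No cut-off is given.

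The only model-based analysis is reserved for other variables: "Linear mixed-effects models will be used to assess changes in nutritional variables from baseline to follow-up visits". The section does not say whether those models adjust for baseline.

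The Sample Size section fits an unadjusted comparison of change. It aims "To detect a difference of 1 unit on the PASI scale", "with an α risk of 0.05" and a two-sided test, and for the spread it says "we anticipate the SD in PASI reduction at week 16 to be much lower, around 1". It arrives at 19 per group after a 15% allowance for loss to follow-up.

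The Roles section says that the coinvestigators who analyse the data are blinded to group.

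**The concern.** Baseline PASI is measured on every patient, and eligibility allows values from 2 to 10. A patient who enters at 2 can improve by at most 2 points, so the amount of change can be expected to depend on the starting value. A test on change scores deals with baseline by subtracting it, which fixes its slope at 1. ANCOVA estimates the slope. Its large-sample variance is never larger, and its estimate is corrected for whatever baseline difference chance has produced between two small arms.

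The second issue is the choice of test. A t test addresses a difference in means, and a rank-sum test addresses a shift in ranks. Because the choice follows sight of the data and has no numerical criterion, the effect measure for the primary outcome is not settled beforehand.

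At stake are power, interpretability if the arms differ at baseline, and a clear primary estimate in a trial of 38 patients whose own discussion concedes that power may be insufficient for some analyses.

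**Working it through.** **Inputs from the protocol article.** Difference 1 PASI unit, SD of change 1, two-sided α 0.05, power at least 80%, loss to follow-up 15%, 19 per arm (Sample Size); baseline PASI 2 to 10 (inclusion criteria).

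**Assumptions, not in the documents.** Correlation ρ between baseline and week-16 PASI of 0.5 to 0.9; equal SDs at both visits.

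**1. The plan's own figure.** Normal approximation: n = 2 × (1.960 + 0.842)² × 1² / 1² = 15.7, so 16 per arm. Allowing for loss, 16 / 0.85 = 18.8, so 19. The stated figure reproduces, on the basis of an unadjusted comparison of change.

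**2. Power of the stated t test.** With 16 evaluable per arm, the noncentrality is 1 / √(2/16) = 2.83 on 30 degrees of freedom. Power is 78.1% (80.7% by the normal approximation).

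**3. Power of ANCOVA.** With equal SDs, residual variance relative to change-score variance is (1 + ρ)/2. Estimating the slope costs one degree of freedom (29 left) and inflates the variance by about 29/28. The noncentrality is 1 / √[(1 + ρ)/2 × 29/28 × 2/16]. Holding the SD of change at 1 also fixes the baseline SD, because SD of change = SD of baseline × √[2(1 − ρ)].

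| ρ | Implied baseline SD | Variance ratio | ANCOVA power, 16 per arm |
|---|---|---|---|
| 0.5 | 1.0 | 0.75 | 87% |
| 0.7 | 1.3 | 0.85 | 83% |
| 0.8 | 1.6 | 0.90 | 81% |
| 0.875 | 2.0 | 0.94 | 79% |
| 0.9 | 2.2 | 0.95 | 79% |

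The comparator is 78% in every row.

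**4. Chance baseline imbalance.** The standard error of the baseline difference at 19 per arm is SD of baseline × √(2/19). A change-score contrast carries (1 − ρ) times the observed imbalance.

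- ρ 0.5, baseline SD 1: standard error 0.32; carried over, 0.5 × 0.32 = 0.16 PASI.
- ρ 0.875, baseline SD 2: standard error 0.65; carried over, 0.125 × 0.65 = 0.08 PASI.

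A one-standard-error imbalance therefore moves the unadjusted contrast by 8% to 16% of the 1-unit target.

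**5. Choice of test.** Simulation under no effect, 16 per arm, 10,000 runs for each distribution. A fixed rule (rank-sum test if a skewness test is significant at 5%) gave type I error of 4.8% for normal and 4.9% for skewed data. Taking whichever test gave the smaller p value gave 5.7% and 6.3%.

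**The case against.** The case for leaving the plan alone is substantial.

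- **The test is valid.** Over randomisations the change-score t test is unbiased, and variation from chance imbalance is already in its standard error. This stands. Imbalance matters only conditionally, for the result in hand, and it is the same loss as the power difference, not an additional one.
- **The gain may be tiny.** If the SD of change is 1 and the baseline SD about 2, ρ is 0.875 and power moves from 78% to 79%. An even spread of baseline values over 2 to 10 would have an SD of 8/√12 = 2.3, which points the same way. This stands, and limits the efficiency argument.
- **A larger bias might be inferred.** Pairing a baseline SD of 2 with ρ 0.5 gives 0.5 × 0.65 = 0.32 PASI, a third of the target. But that pair implies an SD of change of 2 × √(2 × 0.5) = 2, not the plan's 1, so the figure cannot stand beside the plan's power calculation.
- **Analysts could be thought able to steer the p value.** The Roles section says they are blinded, and a fixed rule holds the type I error near 5%. Even free choice of the smaller p value inflates it only to about 6%. What remains is that no rule is fixed.
- **The mixed models might be read as a baseline-adjusted analysis already in place.** The article names them for nutritional variables only and does not mention baseline adjustment.
- **This is a condensed article, and details may sit elsewhere.** Silence on stratification or covariates is no finding. The test rule is different: the article states it, and it is the only between-group rule that can apply to PASI.

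**Conclusion.** The point holds in a limited form. The stated rule is a legitimate analysis and agrees with the sample size, but it is not the best use of the data and does not fix one primary effect measure.

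The efficiency gain from adjustment runs from about 9 percentage points of power (ρ 0.5) to about 1 (ρ 0.875 or above), given an SD of change of 1, equal SDs at both visits and 16 evaluable per arm. Since ρ is unknown, no single value should be quoted as the benefit. The type I error risk from choosing between tests is small. The firmer reasons for change are that the effect measure would be settled in advance and that the estimate would be robust to chance baseline differences. The documents do not support calling the planned result biased or invalid. This is a change that should be made, not one on which the trial's validity depends.

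**What to change.** Before unblinding, replace the test-selection rule for the primary outcome with one prespecified analysis: ANCOVA of week-16 PASI (or, equivalently for the treatment effect, its change) on randomised arm and baseline PASI. Report the adjusted mean difference with a 95% confidence interval. If skewness is a worry, keep a rank-based, permutation or robust-standard-error result as a stated sensitivity analysis that does not replace the primary one. Use the same model for the continuous secondary outcomes, each with its own baseline value.

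The cost is one degree of freedom and a few sentences in the analysis plan. No extra patients, visits or measurements are needed.

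### The unadjusted two-sample test on week-16 PASI change has no stated way to include the 15% of patients expected to be lost, yet the analysis is declared intention to treat

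*Protocol article*

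**What the plan says.** All references are to the protocol article.

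- **Outcomes:** "The primary outcome is the change from baseline in the PASI at week 16".
- **Data Analysis, tests:** differences between the groups are tested by Student t test, or by Wilcoxon rank-sum test where the variable is not normal. PASI is not named in that sentence, but no other between-group method given there would apply to it. No baseline adjustment is stated.
- **Data Analysis, population:** "An intention-to-treat analysis will be performed". No rule for a missing week-16 PASI follows.
- **Data Analysis, models:** "Linear mixed-effects models will be used to assess changes in nutritional variables from baseline to follow-up visits". This is the only use of mixed models that is named.
- **Sample Size:** "We assume a common SD of 1 and estimate a loss-to-follow-up rate of 15" percent, leading to 19 per group.
- **Study Protocol:** all participants attend in person at baseline, week 8 and week 16. Week 8 is a clinical evaluation; the text does not say that PASI is scored then, and Figure 1 is not available.

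**The concern.** Three statements do not fit together once the predicted loss occurs: intention to treat, 15% loss, and a two-sample test on a change score that needs a week-16 value. Run on the observed data, that test compares the patients who reached week 16 and not everyone randomised.

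The loss need not be random. Patients know their arm, and the arms differ in burden and contact: dietary change, free oil and nutritionist calls on one side only. The week-8 visit exists to detect worsening, while eligibility requires topical treatment alone for the whole study, so patients who do badly are among those whose week-16 value might be lost. At stake are whether the primary estimate refers to all randomised patients and whether it is biased.

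The test also makes no use of baseline PASI beyond subtracting it, although eligible patients may start anywhere from 2 to 10.

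**Working it through.** **1. Reproduce the planned size.** Inputs from Sample Size: "To detect a difference of 1 unit on the PASI scale", SD 1, "with an α risk of 0.05", a beta "risk of less than 0.2 in a bilateral contrast", 15% loss.

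- n per group = 2 × (1.960 + 0.842)² × SD² / difference² = 2 × 7.85 = 15.7, so 16.
- 16 / 0.85 = 18.8, so 19 per group and 38 in total. This matches the article.
- The exact t calculation gives 17, then 17 / 0.85 = 20. The difference of one patient per group is not an issue.

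**2. How many would contribute.** 0.85 × 38 = 32.3, about 16 per arm; 38 − 32.3 = 5.7, about 6 absent. With 16 per arm, power is 80.7% (normal approximation), 78.1% (exact t) or about 76% (Wilcoxon on normal data). With all 19 per arm observed, it is 86.9% (normal) or 85.1% (exact t). The size is adequate for its stated purpose; the question is which patients the test describes.

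**3. Direction of bias.** Count improvement as positive. In one arm, completer mean minus all-randomised mean = f × d, where f is the fraction lost and d is completer mean minus dropout mean. The bias in the treatment difference is f(MedDiet) × d(MedDiet) − f(control) × d(control), which can take either sign.

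- *Loss on MedDiet only (assumed):* 16 completers improve by 1 and 3 dropouts by 0. The all-randomised mean is (16 × 1 + 3 × 0) / 19 = 0.84 against 1.00 in completers: an overstatement of 0.16.
- *Mirror case (assumed):* MedDiet is fully observed with mean 1; 16 control completers have change 0 and 3 control dropouts worsen by 1. The all-randomised control mean is −3/19 = −0.16, so the full difference is 1.16 and completers show 1.00: an understatement of 0.16.
- *Range for loss in one arm only:* f from 0.10 to 0.20 and d from 0.5 to 2 give 0.05 to 0.40.

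**4. Loss driven by week-8 response.** A large-sample simulation, all inputs assumed: true difference −0.5 at week 8 and −1 at week 16 (negative is better), SD 1, and patients leave if their week-8 change is worse than a common cut-off set to give 15% loss overall. Loss is then about 21% in control and 9% on MedDiet.

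| Week-8/week-16 correlation | Completers' difference | Estimate using week 8 |
|---|---|---|
| 0.3 | −0.95 | −1.00 |
| 0.5 | −0.91 | −1.00 |
| 0.7 | −0.88 | −1.00 |

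Here the completers' test understates the effect, and an analysis that uses week 8 removes the bias.

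**5. What a mixed model cannot do.** If the three MedDiet dropouts in step 3 left before any post-baseline PASI, a model assuming missing at random would still return about 1.00. Giving them the control-arm mean change (0 in that example) returns 16/19 = 0.84. That is why a sensitivity analysis is needed as well.

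**The case against.** The strongest reply is that this is an omission that the full protocol or an analysis plan may fill. The article never says completers or available data, and a t test after imputation is compatible with intention to treat. That stands as a limit: a reader might infer that the plan prescribes a completers' analysis, and the text does not go that far. It does not dispose of the point, because the article itself chose the test, the population label and the stated scope of the mixed model, and those choices need reconciling.

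Other replies that stand:

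- A reader might infer that mixed models are ruled out for PASI. The article names only nutritional variables but does not claim exclusivity.
- A reader might infer that the completers' test would overstate the benefit. Steps 3 and 4 show that it can go either way. Nothing in the article establishes heavier loss on the diet, which it describes as less aggressive than an earlier dietary study, sets no calorie target and supports with monthly contact.
- A reader might take the inflation from 16 to 19 as itself contradicting intention to treat. It is a routine allowance for lost information and does not define the analysis set.
- Week-8 PASI is unconfirmed. Recruitment closed in October 2024, so if it was not scored it probably cannot be added.

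**Conclusion.** The point holds in limited form. As written, the primary PASI comparison is an unadjusted two-sample test on week-16 change, and the article gives no means of including patients without that value. At the planned 15% loss, about 6 of 38 randomised patients would not contribute unless values are imputed.

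Bias is possible in either direction. The 0.16 PASI in step 3 and the 0.05 to 0.12 in step 4 are illustrations on assumed inputs, not estimates for this trial; the documents give no loss by arm and no correlation between visits. The planned size is not in error. This should be settled before analysis, since the model needed is of a kind the plan already uses.

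**What to change.** Before analysis, while the analysts are still blinded to group as the Roles section provides:

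1. Make the primary PASI analysis a linear mixed model with visit and arm-by-visit terms and baseline means constrained equal across arms, with the arm contrast at week 16 as the primary estimate. Multiple imputation followed by baseline-adjusted ANCOVA is an acceptable alternative.
2. Include all randomised patients with a baseline PASI. Requiring a post-baseline value would again leave out some randomised patients.
3. Include week-8 PASI if it was scored. If it was not, the model still gives baseline adjustment but recovers little information on patients lost before week 16.
4. Add one sensitivity analysis giving MedDiet patients with missing week-16 PASI the control-arm mean change.
5. If the two-sample test on observed changes is kept, call it an available-case analysis and not intention to treat.

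The cost is wording in the analysis section, with no new visits or patients. The downside is that the primary model relies on missing at random; item 4 tests how far the conclusion depends on that.

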The Mediterranean diet (MedDiet) refers to the eating patterns typical of the olive-growing regions around the Mediterranean Sea. This dietary approach emphasizes the consumption of fruits, whole grains, vegetables, nuts, seeds, legumes, and olive oil—the hallmark of the MedDiet. It also includes a moderate intake of red wine with meals, seafood, poultry, and fermented dairy products, while limiting red and processed meats, sweets, and other ultraprocessed foods [11]. Growing evidence suggests that the MedDiet may influence the progression and severity of psoriasis [12,13]. In a 2018 cross-sectional study by Phan et al [14], which included 35,735 participants from the NutriNet-Santé cohort, 3557 participants had psoriasis, with 878 classified as severe cases. The multivariate analysis, adjusted for factors such as age, sex, weight, and cardiovascular risk, showed a significantly lower percentage of severe psoriasis cases among those with greater adherence to the MedDiet [14].

Several research groups have designed large-scale dietary interventions to implement the MedDiet in large patient cohorts. The PREDIMED (Prevention with Mediterranean Diet) study [15], which included 7447 patients at high risk of cardiovascular disease, randomly assigned participants into 3 groups—2 groups received Mediterranean dietary advice supplemented with extra virgin olive oil (EVOO) or a mixture of nuts, while the third group followed low-fat dietary recommendations. All groups were closely monitored by nutritionists. The PREDIMED study demonstrated the positive role of the MedDiet in preventing cardiovascular events. Subsequent satellite studies, such as the PREDIMAR (Prevention of Recurrent Arrhythmias with Mediterranean Diet) study [16], which used an entirely online dietary intervention, further underscored the MedDiet’s benefits and the feasibility of achieving high adherence to this dietary pattern through a dietary intervention.

The MEDIPSO (Impact of the Mediterranean Diet on Patients with Psoriasis) study, detailed in this paper, was conceived to address the need for more evidence on the relationship between psoriasis and the MedDiet. This proof-of-concept randomized controlled trial, inspired by the PREDIMED study, involves a high-intensity MedDiet intervention in patients with psoriasis. The primary objective is to evaluate the impact of this dietary pattern on psoriasis skin involvement, inflammatory cytokines, and quality of life.

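### One unadjusted P<.05 rule covers 41 secondary variables, 25 of them cytokines, and the primary objective in the Introduction does not match the single primary outcome, PASI

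*Protocol article*

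**What the plan says.** All places are in the protocol article.

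- **Data Analysis** ends with a single rule: "Statistical significance will be determined using a 2-tailed level of significance", with P "values less than .05 considered significant". No other threshold appears, and no outcome is exempted or ranked.
- **Outcomes** names one primary outcome: "The primary outcome is the change from baseline in the PASI at week 16". The secondary outcomes follow in five groups: adherence ("Adherence will be assessed using the validated er-MEDAS questionnaire"), anthropometry ("This includes weight, BMI, and abdominal circumference, measured before and after the intervention"), cytokines ("Levels of various ILs and cytokines will be assessed, including granulocyte-macrophage colony-stimulating factor", followed by 24 further analytes), metabolic markers ("changes in serum cholesterol, low-density lipoproteins, high-density lipoproteins, lipoprotein A, apolipoprotein A1, apolipoprotein B, fasting serum insulin, hemoglobin", continuing to A1c and C-reactive protein), and three questionnaires on quality of life, sleep and mood.
- **Sample Size** uses a PASI difference of 1 unit and nothing else.
- **Introduction**, last paragraph: "The primary objective is to evaluate the impact of this dietary pattern on psoriasis skin involvement, inflammatory cytokines, and quality of life".
- **Discussion** and **Strengths and Limitations of This Study** call the trial a proof of concept. The Discussion concedes that power may be insufficient for some analyses. Neither mentions the number of tests.

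**The concern.** Two statements in the article work against each other.

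First, a rule that calls any P below .05 significant, applied to 41 secondary variables, will be expected to produce significant results even if the diet changes none of them. The cytokine panel is the most exposed: it is the largest group, its list is left open by the word including, and the Discussion hopes it will shed light on mechanism.

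Second, Introduction and Outcomes disagree about what the trial primarily tests. Outcomes and Sample Size point to PASI. The Introduction gives cytokines and quality of life equal standing with skin involvement. A reader of the final report would not know from this text whether a cytokine or quality-of-life result bears on the primary question or is secondary.

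At stake is the standing of the secondary claims. A chance cytokine result could be called significant under the stated rule and given weight by the stated objective.

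**Working it through.** **1. The plan's own figure.** Inputs from Sample Size: difference 1, SD 1, two-sided α 0.05, power 0.80, 15% loss.

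n per group = 2 × (1.96 + 0.84)² × 1² / 1² = 15.7, rounded up to 16. With loss: 16 / 0.85 = 18.8, rounded up to 19. This reproduces the stated 19 per group. One PASI comparison at 0.05 accounts for the whole sample size, so no part of it is reserved for cytokines or quality of life.

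**2. Count of secondary variables**, from Outcomes:

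| Group | Number |
|---|---|
| er-MEDAS adherence | 1 |
| Weight, BMI, abdominal circumference | 3 |
| Cytokines named | 25 |
| Metabolic markers (hemoglobin A1c read as one) | 9 |
| Questionnaires | 3 |
| Total | 41 |

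Reading hemoglobin and A1c as two items, and splitting the anxiety and depression scale into two scores, would give 43.

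**3. All nulls true, tests independent.** Expected false positives = 0.05m. Chance of at least one = 1 − 0.95^m.

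- m = 41: 2.05 expected; 1 − 0.95^41 = 0.878.
- m = 25 (cytokines): 1.25 expected; 1 − 0.95^25 = 0.723.
- m = 43: 2.15 expected; 0.890.

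**4. All nulls true, tests correlated.** The article gives no correlations, so these are assumptions. Two-sided normal test statistics with one common correlation r were simulated 100,000 times. Chance of at least one |z| > 1.96:

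| r | 41 tests | 25 cytokines |
|---|---|---|
| 0.3 | 0.75 | 0.61 |
| 0.5 | 0.58 | 0.47 |
| 0.6 | 0.475 | 0.39 |
| 0.7 | 0.375 | 0.32 |
| 0.8 | 0.28 | 0.24 |

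**5. Correlation within groups only.** Adherence is dropped, because the intervention targets it directly and its null is implausible. That leaves 40 tests. Assumed correlations are 0.8 for anthropometry, 0.4 for metabolic markers and 0.5 for questionnaires, with none between groups. The chance is 0.78 with cytokine correlation 0.3, 0.70 at 0.5, 0.62 at 0.7 and 0.54 at 0.9.

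**6. Only cytokines and questionnaires null** (28 tests, same assumptions): 0.66 at cytokine correlation 0.3, 0.535 at 0.5, 0.40 at 0.7 and 0.27 at 0.9.

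**7. The primary test.** PASI at week 16 is one test at 0.05. Nothing above changes its error rate.

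**The case against.** The strongest reply is that this is a condensed article. A multiplicity scheme usually sits in an analysis plan, which is not shown, and the P<.05 sentence may be no more than a general convention. The mere absence of a scheme would indeed be no finding. But the sentence is in the text and carries no restriction, so an analysis plan with a scheme would have to override it. The mismatch between objective and primary outcome is also in the published text.

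A second reply is that the Methods are clear: Outcomes names PASI alone and Sample Size follows it. The Abstract's objective and Study Design list the same domains without calling them primary. This stands, and it limits the mismatch to one sentence in the Introduction that needs aligning.

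A third reply is that unadjusted secondary testing is common in a proof-of-concept trial. That is fair, but such results are then usually labelled exploratory. Here the rule calls them significant.

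A reader might also infer more than the article supports:

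- **That a false positive is more likely than not.** This needs all or most nulls to be true and no strong correlation. The cytokine figure is already 47% at r = 0.5, and the 41-test figure drops below half at about r = 0.6. Independence cannot hold throughout, since weight and BMI change together in adults.
- **That the objective's wording raises the error rate.** It changes no probability. It affects only the weight a cytokine or quality-of-life result might be given.
- **That chance cytokine results will determine the next trial.** The article links planning of larger trials to logistical and methodological lessons. No passage says that cytokine P values will select hypotheses or endpoints.

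**Conclusion.** The point holds for the secondary claims and for the stated objective, not for the primary test. Following the rule as written gives 1.25 expected false significant cytokines and 2.05 across the 41 variables if all nulls are true; these expectations do not depend on correlation. The chance of at least one is up to 72% and 88% respectively under independence. It falls to 47% and 58% at an assumed common correlation of 0.5, and to 24% and 28% at 0.8. Over that range it stays well above 5%. These figures rest on true nulls and on assumed correlations, because the article supplies none. The PASI comparison keeps its 5% type I error, and its sample size reproduces. The change is worth making before the analysis is run, but it does not threaten the main result.

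**What to change.** - In Data Analysis, state that the comparison of PASI change at week 16 is the only confirmatory test at 0.05.
- Reword the objective in the Introduction so that skin involvement measured by PASI is primary, and cytokines and quality of life are secondary, as in Outcomes.
- Apply false discovery rate control within the 25-cytokine panel, for example Benjamini-Hochberg at 5%. The k-th smallest P value is then compared with 0.05k/25 = 0.002k, so a single isolated result needs P ≤ 0.002. Other schemes would also serve; what matters is that one is fixed in advance.
- Label the secondary outcomes exploratory and report each as an estimate with a 95% confidence interval.

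The cost is wording only: no added participants, visits or samples, and no effect on the power for PASI. The small downside is that fewer cytokine results may be called significant.
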